## Abstract

**Background::**

Nonalcoholic fatty liver disease (NAFLD) has emerged as a major health problem worldwide; according to statistics, 10% to 25% of patients with NAFLD can progress to nonalcoholic steatohepatitis (NASH). A link between the composition and metabolites of intestinal microbiota and the development of NAFLD is becoming clearer. It is believed that microbiota factors are driving forces of hepatic steatosis and inflammation. The formulated food that contains prebiotics and dietary fiber may improve NAFLD by altering the intestinal flora and its metabolites.

**Methods::**

The study plan to recruit adult patients (18–75 years, n = 120) with NAFLD, range of alanine aminotransferase is 1.5 to 5 times upper limit of normal (ULN) or liver biopsy is confirmed as NASH. Participants will be randomly allocated into 2 groups: formulated food (n = 80) and a placebo group (n = 40) for 24 weeks. Both groups will receive lifestyle and nutritional advice. The primary endpoint is a decrease in MRS-PDFF by more than 30% from baseline at 24 weeks. The secondary endpoints include the change of anthropometric, liver function, glycolipid metabolism, and systemic inflammation at 4, 12, and 24 weeks. In addition, we consider the changes in intestinal microbiota as an exploration to assess the abundance and diversity at 24 weeks. Weeks 24 to 36 are the follow-up period of drug withdrawal.

**Discussion::**

This clinical trial will provide evidence of efficacy and safety of formulated food as a potential new therapeutic agent for NAFLD patients.

**Trial Registration::**

The trial is registered in the China Clinical Trial Center (ChiCTR1800016178).

## Introduction

1

Nonalcoholic fatty liver disease (NAFLD) is a chronic progressive liver disease caused by accumulation of intrahepatic fat. With the significant increase in the incidence of obesity and type 2 diabetes, NAFLD has surpassed chronic hepatitis B to become the most common chronic liver disease in China. According to statistics, 10% to 25% of patients with NAFLD can progress to nonalcoholic steatohepatitis (NASH), of which about 20% progress to cirrhosis, and liver cancer have been increasing rapidly in recent years.^[1]^

The current treatment of NAFLD mainly includes Lifestyle intervention: refers to weight control through reasonable diet and exercise. There is evidence that the improvement of liver histology is related to weight loss. When weight loss is 10%, liver histology (steatosis, inflammation, and fibrosis) can be relieved, but due to poor compliance, only 9.9% of patients lose weight within 1 year more than 10%.^[2,3]^ In addition, whether exercise has independent benefits for NAFLD is still inconclusive. Drug therapy: Some drugs such as insulin sensitizers and antioxidants can improve the effect, but they are not approved for the treatment of NAFLD. These drugs have their limitations in treatment. For example, pioglitazone can improve liver steatosis, insulin resistance, and liver enzyme levels, but weight gain of about 3 to 5 kg is the most common adverse reaction,^[4]^ and patients with obvious heart failure also It should not be taken, and it is also related to bladder cancer and bone loss after menopause.^[5–8]^ Human glucagon-like peptide-1 (GLP-1) analogs, such as liraglutide, can suppress appetite, delay gastric emptying, and reduce weight. However, GLP-1 receptors may be downregulated after long-term activation, and the drug may be stopped. Debounce may occur afterwards. In addition, PIVENS studies have shown that antioxidant vitamin E can significantly improve liver inflammation in nondiabetic-NASH patients, but it is not effective for liver fibrosis and is related to the risk of prostate cancer and hemorrhagic stroke,^[9–12]^ so safety needs further evaluation. Surgical treatment: Bariatric surgery can significantly improve inflammation and ballooning, but it is an invasive operation and is not recommended. Therefore, the actual treatment of NAFLD has not been resolved.

Current studies have shown that the occurrence and development of NAFLD are closely related to the composition and metabolites of the intestinal flora.^[13]^ In obese patients, the diversity and abundance of intestinal microbes have undergone significant changes, prone to overgrowth of small intestinal bacteria, increased intestinal permeability, and increased absorption of endotoxins,^[14,15]^ thereby activating the NF-kB pathway and its related inflammatory pathways increase the possibility of NAFLD formation.^[16,17]^

It has been projected that dietary factors play a more important role in shaping the composition of the gut microbiota.^[18]^ At present, it is mainly regulated by probiotics, prebiotics, and synbiotics. Prebiotics are defined as “a selective fermentation component that causes a specific change in the composition and/or activity of the gastrointestinal microbiota to confer a host's health benefit.”^[19]^ In pig microbiome analysis, high-fiber/low-fat diet is associated with higher concentration of *Bifidobacteria*, *Lactobacilli*, and *Faecalibacterium prausnitzii*, which have a protective role in intestinal inflammation.^[20]^ This phenomenon also exists in a human experimental research that healthy subjects with improved glucose metabolism following fiber supplementation have a higher *Prevotella/Bacteroides* ratio than those who do not respond to increased fiber.^[21]^

Fermentation of fiber by gut microbiota yields SCFAs that not only provide energy for the host but also play an immune regulatory role. Recent studies have shown that SCFAs exerts anti-inflammatory and immune effects through the effects on Treg cell expansion/generation via SCFAs-GPCR or their HDAC-inhibiting ability.^[22]^ Prebiotics can also improve intestinal barrier function and alleviate inflammation and insulin resistance associated with obesity by increasing gut hormone release, such as glucagon-like peptides 1 and 2 (GLP-1 and GLP-2), and by regulating endogenous cannabinoid systems.^[13,23,24]^ In addition, Bomhof et al^[25]^ through liver biopsy follow-up found that the overall NAS score decreased after taking prebiotics.

These results suggest that improving the gut microbiota by taking dietary supplements may be a potential treatment for patients with NAFLD. The most commonly used prebiotics in practice are oligofructose, galacto-oligosaccharide, lactulose and nondigestible carbohydrate inulin, cellulose, resistant starch, hemicellulose, gums, and pectin, while formulated food is rich in prebiotics, mainly oligofructose, isomalto-oligosaccharide, and dextrin. Therefore, we designed a randomized, double-blind, placebo-controlled trial to evaluate the role of formulated food in improving NAFLD.

## Methods

2

### Trial design

2.1

The aim of the trial is to evaluate the efficacy and safety of formulated food 2 packs per day vs placebo for 24 weeks in NAFLD. During this time, subjects need to visit the hospital regularly and comply with an individualized diet and lifestyle provided by a professional dietitian, at the same time increasing exercise, the frequency is maintained 4 to 5 times a week, 40 minutes each time. Dietary intake at these stages will be recorded by an app for easy management assessment. The study plans to recruit 120 adult NAFLD patients from the Affiliated Hospital of Hangzhou Normal University, randomly assigned.

### Ethical considerations and registration

2.2

The study protocol is in line with the Helsinki Declaration and related laws. We conducted an ethical review in accordance with this declaration and regulations, and the trial was approved by the Ethics Committee of the Hangzhou Normal University Affiliated Hospital. The trial was also registered with the China Clinical Trial Center with registration number ChiCTR1800016178. All subjects will sign a written informed consent form and retain a copy before receiving treatment, which have been approved by the qualified Ethics Committee. During and after the study, we will follow the requirements of the Ethics Committee.

### Eligibility

2.3

In the NAFLD patients enrolled in this study, we require ALT>1.5ULN or liver biopsy to confirm NASH with a 25 kg/m^2^< BMI <35 kg/m^2^. In addition, we excluded patients who had been taking drugs, which can influence ALT in the past 3 months. Detailed enrollment and exclusion criteria are summarized in Tables 1 and 2.

**Table 1 T1:** Inclusion criteria.

Criteria type	Description of inclusion criteria
Sex	Men and women
Age	18–75 yr
Alcohol consumption	No history of significant alcohol consumption (<70 g/wk for women and < 140 g/wk for men)
Body mass index	25 kg/m^2^<BMI<35 kg/m^2^
Evidence of NAFLD	ALT>1.5×ULN at the start of this study, or liver biopsy to confirm NAFLD
Blood pressure	Hypertension patients will be required to take a stable antihypertensive drug(s) to keep blood pressure stable (<140/90 mm Hg) 2 mo before randomization, patients may continue to take antihypertensive drug(s) during clinical trials
Blood lipid	If a participant is using a statin or fibrate, he/she will be required to be on a fixed dose to keep lipids stable within 3 mo before enrollment
Other drug use	The following medications were not received within 3 mo before enrollment (metformin, thiazolidinediones, hypoglycemic agents, DPP-4 inhibitors, GLP-1, SGLT2 inhibitors, polyene phosphatidylcholine, glycyrrhizin preparation, bicyclol, reduced glutathione, S-adenosylmethionine, silymarin, OCA/UDCA, betaine, fish oil, phosphodiesterase inhibitor, gemfibrozil)
Informed consent	Understand the study and sign an informed consent form

BMI = body mass index, ALT = alanine aminotransferase, DPP-4 = dipeptidyl peptidase-4, GLP-1 = glucagon-like peptide-1, SGLT2 = sodium-dependent glucose transporters 2, OCA = obeticholic acid, UDCA = ursodeoxycholic acid.

**Table 2 T2:** Exclusion criteria.

Criteria type	Description of exclusion criteria
Alcohol consumption	Alcohol and/or drugs abuse and dependence over the past 5 yr History of significant alcohol consumption (>10 g/day for women and >20 g/day for men)
Liver comorbidities	Patients with cirrhosis Patients with any other acute or chronic active liver diseases such as viral hepatitis, hereditary hemochromatosis, hepatolenticular degeneration, alpha-antitrypsin deficiency, alcoholic liver disease, drug-induced liver diseases, etc
Other comorbidities	Known heart failure of New York Heart Association class 2, 3, or 4 Known acceptance of cardiac pacemaker implantation Uncontrollable hypertension With uncontrolled hypothyroidism (serum level of thyroid-stimulating hormone is 2 times higher than the upper limit of normal value) Renal insufficiency, serum creatinine > upper limit of normal Evidence of positive human immunodeficiency virus antigen or antibody (HIV-Ag/Ab)
Other	Pregnant or lactating women Female early pregnancy screening test positive, or unwilling to contraception during clinical trials Cannot accept MRI examiners Other investigators believe that clinical trials cannot be completed Those who cannot sign informed consent

### Study flow and schedule

2.4

The flow chart of the study is shown in Figure 1, and the study schedule is summarized in Table 3. For study visits at week 0, week 4, week 12, week 24, week 36 patients must fast for 8 hours before the visit, and then take blood for metabolic assessment. Body weight, waist circumference, and hip circumference will be measured at each visit. In order to better assess patient compliance, we require that remaining meal powders be returned at each study visit and will be counted by drug administrators to further reduce the likelihood of unblinding.

**Figure 1 F1:**
[figure not shown]
Study design.

**Table 3 T3:** Objectives and procedures.

	Study time point, wk				
	Treatment period				Follow-up period
Study objectives	0	4	12	24	36
Primary objectives					
Change in liver fat content (MRS/MRI-PDFF)	×		×	×	
Secondary objectives					
Change in anthropological indicators (BMI and WHR)	×	×	×	×	×
Change in liver function (ALT, AST, GGT)	×	×	×	×	×
Change in diabetic factors (FPG, FINS, HOMA-IR, HbA1c)	×	×	×	×	×
Change in lipids (TG, TC, HDL-C, LDL-C)	×	×	×	×	×
Change in IL-6 and CK18	×	×	×	×	×
Change in HRQOL (SF-36)	×			×	
Assessment of diet and exercise	×	×	×	×	
Record distribute and recycle of drug	×	×	×	×	
Record of drug combination	×	×	×	×	
Safety objectives					
Renal function (BUN, Cr, eGFR)	×	×	×	×	×
Blood routine	×	×	×	×	×
Urine routine	×	×	×	×	×
Fecal routine	×				
Coagulation function	×				
TSH	×				
Virus	×				
Blood HCG	×				
ECG	×			×	
Exploratory endpoint					
Change in intestinal flora	×			×	

All objectives will be compared between formulated food and placebo. ALT = alanine aminotransferase, AST = aspartate aminotransferase, BMI = body mass index, CK18 = cytokeratin 18, Cr = creatinine, eGFR = estimated glomerular filtration rate, ECG = Electrocardiogram, FINS = fasting insulin, FPG = fasting plasma glucose, GGT = γ-glutamyl transferase, HbA1c = glycosylated hemoglobin A1c, HCG = human chorionic gonadotropin, HDL-C = high-density lipoprotein-cholesterol, HOMA-IR = homeostasis model assessment insulin resistance, HRQOL = health-related quality of life, IL-6 = interleukin-6, LDL-C = low-density lipoprotein-cholesterol, PDFF = proton density fat fraction, TC = total cholesterol, TG = triglycerides, TSH = thyroid-stimulating hormone, WHR = waist to hip ratio.

### Dosing rationale

2.5

In the pre-test, patients took 40 g formulated food every day for 12 weeks without any adverse drug reactions, including diarrhea, nausea, constipation, and so on. Therefore, this test selected dose of formulated food 40 g/day to avoid adverse reactions.

### Randomization, masking and adverse events

2.6

Subjects should be screened before signing informed consent to determine if they meet the inclusion criteria and do not meet any exclusion criteria. Subjects will be randomly assigned to receive formulated food or placebo, and the distribution of the drug will be kept confidential to the investigator and subject. The drug manager will assign a drug or placebo to each patient during the follow-up period. All test drugs are packaged identically. Until the end of the trial, all subjects and investigators were blinded to the specific allocation of the drug. Adverse events (AEs) will be closely monitored throughout the course of the study and all AEs will be recorded in the case report form. If a serious AE occurs and the study drug is suspected to be a potential cause, the drug manager will only open the assignment information to the doctor in attendance.

### Supply of formulated food and placebo

2.7

Only the person responsible for registering the patient knows the distribution of the drug and ensures that the subject is double-blind with the investigator. Formulated food and placebo are indistinguishable in appearance. They are manufactured and supplied by Jintong Special Medical Food Co., Ltd. (Guangzhou, China) and are not commercially available. We generated 120 nonrepeating random numbers through SPSS, and randomly assigned them to the formulated food group and the placebo group. Each number corresponding to a serial number. Subjects get unique serial number according to the time of enrollment that determines which group he or she is. Double-blind will remain throughout the study and all study data will be kept confidential until all subjects complete the 36-week study.

### Efficacy and safety evaluation

2.8

#### Primary endpoints

2.8.1

The study endpoints are summarized in Table 4. The primary endpoint is a decrease in MRS-PDFF by more than 30% from baseline at 24 weeks. MRS-PDFF and MRI-PDFF are closely related to liver fat content assessed by liver biopsy, with no superiority between them. Preliminary results from a phase II clinical trial confirmed the feasibility of MRI-PDFF in longitudinal observation of clinical trials and highlighted the evidence that liver stiffness by MRI-PDFF is a biomarker of steatosis. In addition, data confirm that changes in MRI-PDFF are associated with hepatic steatosis and overall NAS score response. At the same time, MRI achieves 100% accuracy by a fat fraction threshold of 5.56% to distinguish normal and abnormal fat fractions in liver steatosis testing as long as all known confounding factors are resolved. Therefore, MRS-PDFF and MRI-PDFF potentially replace liver biopsy to assess liver fat content.^[26–28]^

**Table 4 T4:** Study endpoints.

Primary endpoints
<Efficacy endpoints>
Change in liver fat content (MRS/MRI-PDFF) from baseline at 24 wks
Secondary endpoints
<Efficacy endpoints>
Change in anthropological indicators (BMI, WHR) from baseline at 4,12,24 wks and at the time of drug discontinuation
Change in liver function biomarkers (ALT, AST, GGT) from baseline at 4,12, 24 weeks and at the time of drug discontinuation
Change in diabetic biomarkers (FPG, FINS, HOMA-IR, HbA1c) from baseline at 4,12, 24 wks and at the time of drug discontinuation
Change in lipid biomarkers (TG, TC, HDL-c, LDL-C) from baseline at 4,12, 24 wks and at the time of drug discontinuation
Change in IL-6 and CK18 from baseline at 4,12, 24 wks and at the time of drug discontinuation
Change in HRQOL using SF-36 from baseline at 24 wks
< Safety endpoints>
Change in blood tests of renal function (BUN, Cr, eGFR) from baseline at 4,12,24 wks
< Exploratory endpoint>
Changes of intestinal flora abundance and diversity from baseline at 24 wks

ALP = alkaline phosphatase, ALT = alanine aminotransferase, AST = aspartate aminotransferase: BMI = body mass index, CK18,cytokeratin 18, Cr = creatinine, eGFR = estimated glomerular filtration rate, FINS = fasting insulin, FPG = fasting plasma glucose, GGT = γ-glutamyl transferase, HbA1c = glycosylated hemoglobin A1c, HDL-C = high-density lipoprotein-cholesterol, HOMA-IR = homeostasis model assessment insulin resistance, HRQOL = health-related quality of life, IL-6 = interleukin-6, LDL-C = low-density lipoprotein-cholesterol, PDFF = proton density fat fraction, TC = total cholesterol, TG = triglycerides, WHR = waist to hip ratio. Placebo vs formulated food.

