### Sample size estimation

2.10

The sample size was calculated using Medcalc version 18.2.1 software. On the basis of the results of the pre-test, we expected the formulated food to improve the ratio by about 50% and about 13% in the placebo group, with an α level of 2-sided type I error of 0.05, with a β level of type II error of 0.02. The placebo group was calculated to be 35 patients. Because the formulated food group vs the placebo group is 2:1, the total number is about 120 taking into account the 10% shedding rate.

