### Statistical analyses

2.11

This study will use intent-to-treat patient population. Values with a bias distribution will be log transformed before analysis. Baseline characteristics, categorical variables will be tested by χ^2^, and continuous variables will be compared by *t* test. Repeated measures analysis of variance (ANOVA) will be used for variables measured over time to test treatment efficacy, time, and interaction between them. To compare differences between baseline and 24 weeks, paired *t* tests will be used for primary and secondary outcomes (liver function biomarkers, diabetic biomarkers, liver fat content, diabetic biomarkers, lipid biomarkers, BMI, WHR). Secondary analysis will be performed in all participants who completed 24 weeks of intervention and had a drug intake rate of ≥80%, and cases with missing data would be excluded from the analysis. In all analyses, a 2-sided *P* value 0.05 will be considered significant. The frequency of the AE will be assessed using a χ^2^ test.

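### The primary endpoint is a >30% MRS-PDFF response in the text and sample size, but an unthresholded change in MRS/MRI-PDFF in Tables 3 and 4, with a paired t test in section 2.11

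*Protocol article*

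**What the plan says.** Section 2.8.1 states: "The primary endpoint is a decrease in MRS-PDFF by more than 30% from baseline at 24 weeks". The abstract says the same. This is a yes/no outcome per patient, on one modality.

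Section 2.8.1 also says that Table 4 summarises the endpoints. The only primary entry there is "Change in liver fat content (MRS/MRI-PDFF) from baseline at 24 wks". Table 3 lists the primary objective in the same terms, with scans at weeks 0, 12 and 24. Neither table gives a threshold, and both allow either modality. On the modalities, section 2.8.1 says "MRS-PDFF and MRI-PDFF are closely related to liver fat content assessed by liver biopsy, with no superiority between them".

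Section 2.10 sizes the trial on two rates: "we expected the formulated food to improve the ratio by about 50% and about 13% in the placebo group".

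Section 2.11 says: "To compare differences between baseline and 24 weeks, paired *t* tests will be used for primary and secondary outcomes", and its list of variables includes liver fat content. It also plans repeated measures ANOVA for variables measured over time. Chi-square tests appear only for categorical baseline characteristics and for adverse events ("The frequency of the AE will be assessed using a χ^2^ test").

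**The concern.** A trial's confirmatory claim needs one scale, one threshold and one measurement method. This document gives two versions of the primary endpoint. The responder version is supported by the abstract, section 2.8.1 and the sample size. The change version is supported by Tables 3 and 4 and section 2.11.

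Two things are at stake. First, if significance on either version can be called the primary result, the chance of a false positive exceeds the nominal 5%. Second, the responder endpoint has no between-group test assigned to it, while the change endpoint has no stated effect size or SD behind the sample size. The modality label adds a lesser problem: nothing shown requires the same method at baseline and week 24, and a difference between methods would enter the percentage change that decides response.

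**Working it through.** **1. Which endpoint was the trial sized on?** Inputs from section 2.10: rates 0.13 (placebo) and 0.50 (formulated food), two-sided α 0.05 (z = 1.960), β 0.02 (z = 2.054), allocation 2:1 (k = 2), 10% loss.

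Pooled rate: p̄ = (0.13 + 2 × 0.50)/3 = 0.3767.

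n(placebo) = [1.960 × √(p̄(1 − p̄)(1 + 1/k)) + 2.054 × √(0.13 × 0.87 + 0.50 × 0.50/k)]² / 0.37²

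= [1.163 + 1.002]² / 0.1369 = 34.2, rounded up to 35.

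This matches the stated 35. The total is 35 + 70 = 105, and 105/0.90 = 117, or about 120. The sample size is a two-proportion calculation and agrees with the responder endpoint.

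**2. Can the same number be tied to the change endpoint?** No. The document gives no expected mean difference and no SD for PDFF. With 35 and 70 evaluable patients, the detectable standardised difference is (1.960 + z of the power) × √(1/35 + 1/70): 0.58 SD at 80% power, 0.67 SD at 90% and 0.83 SD at 98%. Nothing in the document says whether such differences are expected.

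**3. Do the parts of the document agree?**

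| Place | Scale | Modality |
|---|---|---|
| Abstract, section 2.8.1 | >30% decrease (responder) | MRS |
| Section 2.10 | Two proportions | Not stated |
| Tables 3 and 4 | Change, no threshold | MRS/MRI |
| Section 2.11 | Paired t test (continuous) | Not stated |

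**4. What does a free choice of scale cost?** Assumptions, none of them from the document except the arm sizes: 80 vs 40 patients; baseline PDFF median 15% with log-SD 0.4; relative change of mean −10% and SD 30% in both arms; independent scan noise of 0.25 to 1.5 percentage points; between-group tests at two-sided 0.05; 20,000 null trials per setting.

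- Each single test: about 5%.
- Responder test or change test, one modality: about 8–9% across the noise range (8.4% at 1 point).
- Any of two scales × two modalities, if every patient had both scans: 10.5% at 0.25 points, 10.8% at 0.5, 12.2% at 1 and 13.1% at 1.5.

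**5. What would a change of modality within a patient do?** Take the same relative change, ignore scan noise, and let MRI, used at week 24 only, read a fraction b below MRS. A patient then counts as a responder when the true ratio is below 0.70/(1 − b).

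- b = 0: Φ((0.700 − 0.90)/0.30) = 25%.
- b = 0.05: Φ((0.737 − 0.90)/0.30) = 29%.
- b = 0.10: Φ((0.778 − 0.90)/0.30) = 34%.

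The values of b are illustrative; the document gives none.

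**The case against.** The strongest reply is that the intended endpoint is clear enough. The abstract, section 2.8.1 and the sample size all point to the responder definition. Nearly every efficacy row of Table 4 begins with the word change, so the primary row may be only a label for the measured variable. This has force for Table 4 alone: it says change, not mean change, and the continuous reading is an inference. But section 2.11 supports that inference by assigning paired t tests to the primary outcome and listing liver fat content. A paired t test cannot analyse a responder proportion.

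A second reply is that an analysis plan not shown may settle the matter. It may well fix modality and scan consistency, which a condensed article can leave out. On scale, however, the article is not silent: it states two definitions, and any analysis plan would have to overrule one of them.

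A third reply concerns the simulation. It compares arms, whereas the paired t test in section 2.11 is a within-group comparison. The repeated measures ANOVA could supply a between-group test, but also on the continuous scale. The error rates therefore describe a plausible between-group analysis, not the exact tests named.

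Three stronger readings are tempting and are not supported. A reader might infer that four candidate tests are available; that needs both MRS and MRI in every patient, and MRS/MRI may equally mean one or the other. A reader might infer that mixing modalities biases the comparison; a switch unrelated to arm shifts both arms, and sections 2.6 and 2.7 describe blinded subjects and investigators. A reader might infer an intention to choose the endpoint after seeing the data; the document leaves that possible and does not show it.

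**Conclusion.** The contradiction stands and must be resolved before analysis. It lies in the current text and does not depend on the simulation. The sample size is not in error: it reproduces exactly for the responder endpoint.

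The best-supported size of the problem is a false-positive rate of about 8–9% instead of 5%, from the choice of scale alone and under the assumptions listed. The 10–13% range is conditional on dual scanning. Inconsistent modality within a patient would misclassify response (25% becoming about 29% or 34% in the examples) and could move the placebo rate away from the planned 13%, but would not by itself create a difference between arms.

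**What to change.** - **Tables 3 and 4:** state the primary endpoint as the proportion of patients with a relative decrease of more than 30% in MRS-PDFF from baseline at week 24, using the same modality at every scan within a patient. List change in PDFF as secondary and label any MRI-PDFF result as supportive.
- **Section 2.11:** remove the primary outcome from the paired t tests. Name a between-group comparison of proportions, for example a chi-square test, in the intent-to-treat population. Editing the tables alone would leave a within-group t test assigned to a binary endpoint.

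The cost is a text amendment to two tables and one section. The sample size stays at about 120 and no scans are added.
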